| It is important to store the data securely and used in a way its integrity is not compromised. Data obtained from the app will be stored on a local secured cloud platform and only accessible to authorised study team members (PI, co-Is, CRCs, pharmacists). Clinical data will be stored in a secure database, accessible only to the PI, co-Is, CRCs, pharmacists. The use of the data from the study will be controlled by the PI. |
| **SAMPLE SIZE AND STATISTICAL METHODS** |
| Determination of Sample Size |
| A total of 376 patients (188 per arm) are to be recruited. The computation takes into account a) 5 level of significance, b) desired statistical power of at least 90%, c) the potential application of a mixed-effect model in view of the multi-centre design, and to cater for the random effects of repeated measurements, d) a small effect size to be detected (i.e., <0.2), e) fewer than 10 predictors to be accommodated in model building and f) no more than 20% drop outs. A post-hoc power calculation should be facilitated after the data analysis is performed. |
| Statistical and Analytical Plans |

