| The data collected will be screened for accuracy, missing data, outliers, and statistical assumptions. Following the principles of intention-to-treat (ITT) analysis, individuals will be retained in the group they were randomized to. At each measurement time, efforts will be made to minimize missing outcome data, and the reasons for individuals' loss of follow-up will be recorded. Missing data will be imputed using averages of answered items with no more than 20% missing data. When more than 20% of the items are missing, the overall score is not computed, and the data is considered missing. Sensitivity analyses will also be performed to determine the robustness of the assumption about missing data.  Descriptive statistics of baseline and follow-up data will be reported by mean and standard deviation for normally distributed variables, median and interquartile range for non-normally distributed variables, and proportions (count and percentage) for categorical variables. Continuous variables that are not normally distributed will be approximately normalised by using transformations and categorisations whenever applicable. Between group comparisons (by gender, age group, years since diagnosis, etc) will be made using Pearson χ2 or Fisher's exact test for categorical data, whereas continuous data will be tested with independent t-test and Mann–Whitney U test to evaluate changes between baseline and end-of-trial measures.  This study will also include regression/ modelling analyses to adjust potential confounders in this study such as gender, disease duration, number of comorbidities, and hypercholesterolemia treatment modalities (statins only, or ezetimibe, or statins plus ezetimibe). Subgroup analysis may be performed if the potential confounders found to be significant.  STATA (StataCorp Statistics for Windows, Version X, College Station, Texas) and R version X (The R Foundation for Statistical Computing; Vienna, Austria) will be used for all statistical analysis. All statistical tests will be performed using two-sided tests at the 0.05 significance level. |

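### Section 10.1 claims at least 90% power for a small effect below 0.2, but names no metric, outcome, time point or correlation, and 376 does not follow from its stated inputs

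*Protocol*

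**What the plan says.** Protocol section 10.1 (Determination of Sample Size) fixes the size: "A total of 376 patients (188 per arm) are to be recruited". It says the computation took six things into account:

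- a "5 level of significance" (read here as 5%);
- a "desired statistical power of at least 90" percent;
- "the potential application of a mixed-effect model in view of the multi-centre design, and to cater for the random effects of repeated measurements";
- "a small effect size to be detected (i.e., <0.2");
- "fewer than 10 predictors to be accommodated in model building";
- drop-out of at most 20%.

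The section ends: "A post-hoc power calculation should be facilitated after the data analysis is performed".

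Section 10.2 sets the sidedness: "All statistical tests will be performed using two-sided tests at the 0.05 significance level". For continuous outcomes it names a t-test or Mann-Whitney test on change from baseline to end of trial, with regression adjustment in addition. The primary objective in section 2 is adherence at 6 and 12 months. Table 1 schedules the DOSE measure at months 0, 3, 6 and 12, and pill counts at months 3, 6 and 12.

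**The concern.** A power statement needs an effect size on a named scale, for a named outcome and time point. Here the effect is only bounded from above. An inequality with no lower limit cannot be met by any finite sample, and 0.2 is its most favourable value. Read in the usual way, as a standardised mean difference, 0.2 needs a far larger trial than 376 for 90% power in a simple two-arm comparison.

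At stake is how the result is interpreted. With the text as it stands, a null finding could be reported as excluding even a small effect with 90% power, when the comparison might well have missed such an effect. The closing request for a post-hoc power calculation adds to the risk if that calculation uses the observed effect.

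**Working it through.** **Inputs.** From section 10.1: 188 per arm, 90% power, 20% loss, so 188 × 0.8 = 150.4, or about 150 completers per arm. From section 10.2: two-sided 0.05. Taking 0.2 as an SD-unit difference *d* is an assumption, as is every correlation ρ below.

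**1. Which effect gives the plan's figure?** n per arm = 2(1.960 + 1.282)²/d² = 2 × 10.507/d².
- d = 0.375: 21.015/0.1406 = 149.4, so 150; 150/0.8 = 187.5, so 188 per arm and 376 in total. This matches.
- d = 0.2: 21.015/0.04 = 525.4, so 526; 526/0.8 = 657.5, so 658 per arm and 1,316 in total. This does not.

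**2. Power of a single unadjusted comparison** (noncentral t, noncentrality d√(n/2)).

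| d | 150 per arm | 188 per arm |
|---|---|---|
| 0.20 | 41% | 49% |
| 0.15 | 25% | 31% |
| 0.10 | 14% | 16% |

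The difference detectable at 90% power is 3.2415 × √(2/n): 0.374 SD for n = 150 (0.376 by noncentral t) and 0.334 SD for n = 188.

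**3. Change-score t-test named in section 10.2.** The variance factor is 2(1 − ρ). At ρ = 0.5 the factor is 1, so power at 0.2 SD is again 41%.

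**4. Baseline adjustment and repeated measurements.** For the baseline-adjusted mean of m follow-up visits with equal correlation ρ, the variance factor is (1 + (m − 1)ρ)/m − ρ². With 150 per arm and d = 0.2:

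| Analysis | Factor at ρ = 0.5 | Power at ρ = 0.5 | ρ needed for 90% |
|---|---|---|---|
| One visit | 0.750 | 51% | about 0.85 |
| Mean of three visits | 0.417 | 76% | about 0.735 |

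For the three-visit mean, power is about 74% at ρ = 0.3. The difference detectable at 90% for one adjusted visit at ρ = 0.5 is 0.374 × √0.75 = 0.32 SD.

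**5. Other effect-size metrics.** For two equal arms d = 2f and f² is the square of f.
- f = 0.1875, one measurement: 302 completers, 378 after dividing by 0.8. This is essentially 376, but d = 2 × 0.1875 = 0.375.
- f = 0.15, four measurements, ρ = 0.5: 294 completers, 368 after dividing by 0.8. Here d = 0.30. Four measurements would have to include month 0, when no intervention effect can exist. With the three follow-ups alone, 314 completers are needed, 393 after dividing by 0.8.
- f² = 0.035, one coefficient: 90% power with 300 completers. Here d = 2√0.035 = 0.374.

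**6. Post-hoc power.** Computed from the observed effect, power is approximately Φ(|z| − 1.96), where z is the observed test statistic (ignoring the negligible other tail). It is therefore fixed by the p-value: at p = 0.05 it is Φ(0) = 50%, whatever the sample size.

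**The case against.** The strongest reply is that section 10.1 never says 0.2 is in SD units, and that it lists a mixed model for repeated measurements among its inputs. The limit on predictors also points to a regression-type calculation, where f² is a usual metric. Values of f and f² that satisfy the written inequality do reach 90% power with about 300 completers, and f = 0.1875 essentially reproduces 376. In addition, section 2 does not specify two separate single-visit tests, so an averaged analysis is open.

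Much of this stands. A reader might infer that the trial simply has 41% power, or that it needs 1,316 patients. The document does not support either as an unconditional statement: both rest on an SD scale and a single unadjusted comparison that the protocol does not specify. At 0.2 SD, the analyses considered in the working run from about 41% to 90% as the unstated correlation and model vary.

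What does not stand is the defence of the word small. The f and f² values that fit correspond to about 0.375 SD (f = 0.1875, f² = 0.035) or 0.30 SD (f = 0.15). The mixed model is listed only as a possibility and no correlation is given, so it cannot be credited with a particular gain.

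On post-hoc power, a reader might infer that the plan commits to power from the observed effect. It does not say so; the calculation could use the observed variance or correlation with a planned effect. The criticism applies only to the observed-effect version.

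**Conclusion.** The point holds in conditional form. The stated inputs do not yield 376, because the effect size has no lower limit, metric, outcome, time point or correlation. If 0.2 is a standardised mean difference and the arms are compared once, power is about 41% after 20% loss (49% with none), and 90% power begins at about 0.375 SD. Baseline adjustment and averaging over visits narrow the gap, but deliver 90% at 0.2 SD only if the equal within-patient correlation is about 0.735 (three visits) or 0.85 (one visit), neither of which is stated. Reading the figure as Cohen's f recovers 376 but not the claim of sensitivity to a small effect. This is a fault in the power statement. It is not evidence that 376 is the wrong number of patients, since the protocol does not say which difference would matter.

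**What to change.** Keep 376 patients and rewrite section 10.1 so that it:

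- names the effect-size metric, the primary adherence measure, the time point, the assumed within-patient correlation and the analysis model;
- replaces the small-effect clause with the difference detectable at 90% power, two-sided 5%, under that model. For 150 completers per arm this is about 0.375 SD for a single unadjusted comparison, or about 0.32 SD with baseline adjustment at one visit if the correlation is 0.5. If the sponsor intends a repeated-measures analysis, the figure should be recomputed for it, with the correlation justified;
- deletes the post-hoc power sentence, or at least rules out power computed from the observed effect, and says that the result will be interpreted from the 95% confidence interval set against the restated detectable difference.

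The cost is wording only, with no extra patients. The downside is that the stated sensitivity becomes less favourable than the present text suggests.

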| This study will recruit patients with hyperlipidaemia from National University Polyclinics (NUP) and National Healthcare Group Polyclinics (NHGP). These patients must be deemed to be non-adherent to statins (DOSE score ≥ 1) and have LDL-C level above the recommended target levels (Appendix A. Clinical Guidance for Lipid Management). A total of 376 patients, with 188 patients per arm, will be recruited. |
| Recruitment Process |
| Patients will be recruited by research coordinators positioned in the polyclinics. Primary care team will screen for non adherence to statin using DOSE questionnaire, and if positive and primary care team will verbally explain the study to eligible patients. Should the patient be keen to participate in the study, the primary care provider will refer the patient to the CRC. The CRCs will confirm eligibility according to the inclusion and exclusion criteria. Informed consent will be taken by the polyclinic CRCs after routine clinic follow up and before performance of any study-related procedures (e.g downloading app, administer onboarding questionnaire, Psychometric Battery etc). Patients will then be randomly assigned to the intervention or control group. A centralised team who are not involved in the recruitment or assessment of patients will keep custody of randomization lists. |
| Inclusion Criteria |
| 1. Between 21 to 84 years old 2. Prescribed statins with or without ezetimibe for hyperlipidaemia. 3. LDL-Cholesterol above recommended target level, stratified by risk category (refer to Appendix A) 4. Medication non-adherence as defined by the "Extent to Non-adherence" sub-scale of the DOSE Non-Adherence Measure), with a score > 1 (range from 0-15) 5. Singapore residents (citizens, permanent residents, or long-term pass holders). 6. In possession of a smartphone or tablet with Android or iOS operating systems. 7. Have internet access on their mobile devices. |
| Exclusion Criteria |

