| 1. **Clinical data:** Clinical data will be collected on a patient’s demographic details, past medical history, medication use, blood test results and anthropometric measurements. 2. **Questionnaires**: Onboarding questionnaire, DOSE Non-Adherence Measure and Psychometric Battery Questionnaires will be administered by the CRC 3. **Pill count**: Patients are required to bring along their prescribed lipid-lowering medications during their follow-up visits (@3m, 6m, and 12m). CRC will carry out pill counts with the patients during the visits. 4. **Medical care follow-up**: Standard-of-Care clinical pharmacist will follow-up with patients, titrating lipid-lowering medication (such as statin, ezetimibe etc) as required, and review and take action clinical blood test results (Appendix B; e.g lipid level, blood creatinine kinase and liver function tests where relevant). 5. **Human-AI-health coaching (For intervention only):** Health coach will use the information gathered by the AI chatbot to guide the targeted behavioural intervention during phone consultation. The scope of coaching will be strictly related to the medication adherence and general well-being. The coach will not start, stop, or titrate any medication. Coach will escalate concerns to clinical pharmacists when deemed fit. 6. **Focus group discussion (sub-study):** This will be conducted with a nested sample of 30-50 intervention group patients. The aims are: (a) to collect insights from intervention patients on their experiences with the app and human health coaching, (b) insights into which intervention components work best for them and under what circumstances, (c) insights into concerns which might impact intervention effectiveness, (d) factors that draw their participation and sustained engagement, (e) factors that deter them from sustainable engagement, (f) factors that may lead other CVD patients to be more inclined to partake in such a intervention and (g) ideas and suggestions to make the intervention more appealing and effective. |
|  |
| Randomisation and Blinding |

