| **Pre-screening, recruitment and Visit 1 (month 0)**  Primary care team will screen for non-adherence to statin using DOSE questionnaire, and if positive and primary care team will verbally explain the study to eligible patients. Should the patient be keen to participate in the study, the primary care provider will refer the patient to the CRC.  Upon recruitment and after randomisation, patients will be informed if they are allocated to be in the intervention or control group. Polyclinic CRCs will email a centralized team who are not involved in the screening and assessment of patients for the randomization outcome. Only the centralized team will have access to the randomization list that was pre-generated. The polyclinic CRCs will be blinded until the randomization outcome upon being informed.  CRC will administer the remaining questionnaires and take anthropometric measurements. Lastly, CRC will collect demographic and clinical information from electronic medical record.  **INTERVENTION:** Patients will be required to install the intervention app. The CRC will take the patient through the app features and answer any questions they may have.  Patients will receive curated, reliable and up-to-date medical information in an easily digestible and understandable format via in-app text message. The app can also send reminders via in-app text messages or push notifications to remind patients to take their medicine and their appointment dates. Our Artificial intelligence (AI)–based chatbots will prompt patients to engage in conversation to uncover their barriers to medication adherence and assist with setting personal goals.  **Follow-up Visits (Visit 2 @Month 3, Visit 3 @ Month 6 and Visit 4 @ Month 12**  The CRC will remind patients to bring their lipid-lowering medication before the study visits.  During the visit, the CRC will carry out pill counts, administer questionnaires and collect clinical information from electronic medical record. Anthropometric measurements will be taken at Visit 3 (month 6) only.  Clinical pharmacist will review clinical blood test results, monitor for safety and titrate lipid-lowering medications as required.  **Intervention Group:** Health coach will use the information gathered by the AI-based chatbot, such as patient's readiness to change, perceived barriers and misbeliefs to guide the targeted behavioural intervention via in-app text message or phone consultations. The scope of coaching will be strictly related to the medication adherence and general well-being. The coach will not start, stop, or titrate any medication.  **Focus group discussion (sub-study):** 30-50 Intervention patients who give consent for this substudy will be contacted by study team. The discussion will be held either in-person or virtually and will take approximately 3-4 hours. |

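### Subgroup analyses are triggered by a covariate's significance, not by its interaction with treatment; the treatment-modality covariate also needs its levels and timing fixed

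*Protocol*

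**What the plan says.** Section 10.2 plans regression models to "adjust potential confounders in this study such as gender, disease duration, number of comorbidities". The last item on that list is the lipid-lowering regimen, given three levels: "hypercholesterolemia treatment modalities (statins only, or ezetimibe, or statins plus ezetimibe"). The protocol's next sentence gives the rule for subgroups: "Subgroup analysis may be performed if the potential confounders found to be significant". The section names no treatment-by-covariate interaction, and it sets all tests at the two-sided 0.05 level.

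Three other places bear on the modality covariate:

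- Section 3.3, inclusion criterion 2: "Prescribed statins with or without ezetimibe for hyperlipidaemia".
- Section 6, on medical care follow-up, has the clinical pharmacist "titrating lipid-lowering medication (such as statin, ezetimibe etc) as required". Section 6.3 repeats this for the follow-up visits: "Clinical pharmacist will review clinical blood test results, monitor for safety and titrate lipid-lowering medications as required". Table 1 schedules the pharmacist review in both arms at months 3, 6 and 12.
- Section 6 lists medication use among the clinical data, and Table 1 has clinical data extracted at months 0, 3, 6 and 12. The regimen at entry and the later regimens will therefore all be in the dataset.

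**The concern.** The subgroup sentence uses the wrong evidence. A covariate's main effect answers whether patients at one level do better or worse on average. Subgroup analysis asks whether the difference between arms changes with the level. The first can be large when the second is nil, and the reverse. A trigger built on the first opens subgroups where there is nothing to find and can leave closed those where there is. With no interaction test, the results would probably be read by comparing p-values between levels. At this sample size that often shows one level significant and the other not, even when the effect is identical in both.

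The modality covariate raises a smaller question. One of its three levels cannot occur at entry under criterion 2, and the protocol does not say at what time the variable is read. If a follow-up value were used, the model would condition on something that pharmacists change in response to blood results, and LDL-C at 6 and 12 months is itself a secondary objective. The coefficient for arm would then no longer be the effect of offering the intervention.

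**Working it through.** The plan gives no figure for this rule, so there is none to reproduce. The check asks how the trigger behaves at the planned size.

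**Inputs from the protocol (sections 10.1 and 10.2).** 376 patients, 1:1, at most 20% dropout, two-sided 0.05. Evaluable: 376 × 0.8 = 300.8, taken as 300 (150 per arm).

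**Assumed inputs.** A binary factor split 50:50, a normal outcome with SD 1, and a prognostic effect of 0.4 SD. The treatment effect is set at 0.374 SD, the difference that 150 per arm detects with 90% power: (1.960 + 1.282) × √(2/150) = 3.242 × 0.1155 = 0.374.

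**1. Prognostic factor, no interaction.**
- Standard error of the factor's main effect: 2/√300 = 0.1155.
- Chance that the trigger fires: Φ(0.4/0.1155 − 1.96) = Φ(1.50) = 0.93. Simulations gave 92% to 93%.
- An interaction test fires at its nominal rate, about 5%.

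**2. Uniform true effect of 0.374 SD.**
- Each half has 75 per arm, so the standard error is √(2/75) = 0.1633.
- Power in each half: Φ(0.374/0.1633 − 1.96) = Φ(0.33) = 0.63.
- Chance that exactly one half is significant: 2 × 0.63 × 0.37 = 0.47.
- Chance that this happens and the trigger has also fired: 0.47 × 0.93 = 0.44. Simulated values lay between 44% and 48%, depending on whether the trigger is required.

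**3. True interaction of 0.75 SD, no average covariate effect.** The treatment effect is about 0.75 SD at one level and about 0 at the other, and the covariate's effect averages to zero over the two arms.
- Standard error of the interaction: 4/√300 = 0.231.
- Power of the interaction test: Φ(0.75/0.231 − 1.96) = Φ(1.29) = 0.90.
- The trigger fires in about 5% of trials, because it tests a quantity that is zero.

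This miss depends on the pattern. If the factor is inert in controls and the same interaction appears only under treatment, the average covariate effect is 0.375 SD and the trigger fires in about 89%, much like the interaction test. The trigger is therefore unreliable, not always blind.

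**4. Modality.** Criterion 2 admits two regimens at entry: statin alone, or statin plus ezetimibe. Section 10.2 lists three. The extra level is either a follow-up state or a drafting slip, and the text does not settle which. In illustrative simulations, adjusting for the entry regimen left the treatment estimate essentially unchanged. Adjusting for a follow-up regimen gave anything from no change, or a slight rise, to a fall from 0.375 to 0.318, depending on how strongly escalation was assumed to follow poor adherence. With no true effect there was no bias. None of those inputs is in the protocol, so no size is claimed.

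**The case against.** **The subgroup sentence is permissive, and subgroup lists are usually left to a statistical analysis plan.** Both are true. But the protocol does more than leave the list open: it states a criterion. A later plan that used interaction tests would have to depart from that sentence.

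**A reader might infer that the trigger biases the treatment effect.** It does not. The overall estimate is untouched, and the estimate within a given level is not distorted by the rule. The fault lies in which subgroups are opened and how their contrast is read.

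**A reader might infer that the trigger inflates false subgroup findings.** That is not supported either. In simulated trials with no treatment effect and four binary factors, a significant result in at least one of the eight levels got through the trigger in about 1.5%, 12.5% and 22% of trials for factor effects of 0, 0.2 and 0.4 SD. That is no more than running all eight tests without a trigger. Multiplicity is a general cost of several tests. Four unadjusted interaction tests also carry it: 1 − 0.95⁴ = 18.5%.

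**A reader might infer from the ezetimibe-alone level that a follow-up regimen will enter the model.** The documents do not show this. The variables are called potential confounders, and the others listed are naturally taken at entry. Exclusion criterion 3 also describes background therapy loosely, as statins, ezetimibe or both. A drafting slip fits at least as well. In addition, section 10.2 presents the models as additional to the between-group tests and does not make them primary. What stands is the conflict with criterion 2 and the unstated timing.

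**Conclusion.** The subgroup criterion is wrong as written and should be changed. At 300 evaluable patients, a factor that is only prognostic opens a subgroup analysis in about 92% to 93% of trials, where an interaction test would signal in 5%. A uniform effect of 0.374 SD then looks split between the two halves in roughly 44% to 48%. These figures rest on an assumed 50:50 factor, a 0.4 SD prognostic effect, a normal outcome and the full 20% dropout. A weaker factor would fire the trigger less often. The logical fault does not depend on the numbers. The consequence is data-driven selection and misleading contrasts in an optional analysis, with no bias in the main result.

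The modality point is a clarification. Its levels conflict with inclusion criterion 2 and its timing is open. Adjustment for a regimen titrated during follow-up could attenuate the treatment effect, by an amount that the protocol does not allow to be quantified. Adjustment for the entry regimen carries no such risk.

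**What to change.** Replace the subgroup sentence in section 10.2 with wording such as: *Effect modification will be assessed by treatment-by-covariate interaction terms for a short list of baseline factors named in advance. Interaction estimates with confidence intervals will be reported as exploratory. The significance of a covariate's main effect is not a criterion for subgroup analysis.* Name the factors, for example gender, age group and baseline DOSE score.

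Define the modality covariate as the regimen recorded at randomisation, with two levels (statin alone, statin plus ezetimibe), reconcile it with inclusion criterion 2, and state that no variable measured after randomisation enters the adjustment set.

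The cost is wording only, since medication use is already collected at Visit 1. The downside is power: with 300 evaluable patients and a 50:50 factor, 90% power for an interaction needs a difference between levels of about 3.242 × 0.231 = 0.75 SD. A non-significant interaction will therefore not show that the effect is uniform, and the results must stay exploratory.
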